## 9.5 Randomisation, Blinding and Unblinding

Patients will be randomized to either treatment in a 1:1:1 ratio.

The list of treatment assignments considering the stratification for investigational centre and ASA-class (2 strata:  $ASA \leq 2$  and  $ASA = 3$ ) will be generated by an independent study statistician comprised of consecutive blocks with the order of assignments chosen at random (i.e.: random permuted block of size 3, 6 or 9). The list will be prepared prior to the initiation of the study and will remain with the statistician. Based on this list the statistician will issue sets of random envelopes for each participating hospital, i. e. for the hospital's pharmacies for allocation the patient to the respective treatment and for the Principal Investigators for emergency unblinding (see below). The sponsor will receive a complete set of random envelopes also for emergency situations.

Patients who are eligible for inclusion into the study shall receive an increasing sequential patient number (enrolment number) in accordance with the order of their inclusion in the study. A random number will be issued which includes centre number and strata (A for  $ASA \leq II$ , B for  $ASA = III$ ) and an increasing consecutive number (within the ASA-class stratum). Enrolment of patients will be recorded in the enrolment log (appendix 4: a for stratum A and b for stratum B) A randomization sheet (appendix 5) will be issued with patient's data essential for compilation of the appropriate Investigational Product (Patient ID number, name and birthday – either hand written or use of hospital ID-label –, random number, ASA-class, body weight) and forwarded to the pharmacy to compile the appropriate amount of the respective Investigational Product.

Blinding will be performed by the hospital's pharmacy. In order to maintain blinding the following procedure has to be followed: The maximal possible daily dose for the 6% HES solution is determining the amount of bottles to be compiled for all treatment groups. In the group with HES 10% a balanced crystalloid fluid will be administered (in blinded manner) when the maximum daily dose of HES is reached. Thus, it will be ensured that in all treatment groups are the same amount of bottles (depending on bodyweight).

Example for a 70 kg patient: The maximum daily dose for HES 6% is  $50\text{ml} \times 70\text{kg/d} = 3500\text{ml/d}$ . Thus, 7 bottles with 500ml have to be compiled and will be labelled with sequential number 1 - 7. If according to the stratified randomization list the 70 kg patient has to receive treatment with HES 10% (i. e. maximum daily dose is  $30\text{ml} \times 70\text{kg/d} = 2100\text{ml}$ ) the pharmacist will compile 4 bottles of HES 10% which are labelled with sequential number 1 – 4 and further 3 bottles of crystalloid labelled as bottles 5 – 7. (Note: as bottles contain always 500ml and maximum daily dose of HES is not to be exceeded the amount has to be appropriately rounded down). If according to the stratified randomization list the patient has to be treated with the crystalloid replacement therapy 7 units (numbered 1 – 7) of the electrolyte product will be used.

Bottles always have to be given to the patient in sequential order. This is essential in case not all bottles are required for replacement therapy during surgery and has impact for the group with HES 10%.

For emergency unblinding the statistician will provide sealed envelopes with the patient random number printed to the Principal Investigator (each centre). The envelopes will be sent to the study centre prior start of the study. When breaking the seal of an envelope the respective treatment for the individual patient is stated. The code may only be broken when this is relevant for the safety of the trial subject. Any premature code break (e.g. unblinding due to a Serious Adverse Event, accidental unblinding) should promptly be documented and reported to the Sponsor. Emergency

unblinding may be discussed with the Sponsor prior breaking the seal if possible, i. e. if this is not affecting the patient's safety. Upon study completion all emergency envelopes will be retrieved by the study monitor.

After closure of the database and determination of the analysis populations (in a blinded data review meeting if appropriate) the study will be unblinded.

The population will be stratified with regard to

- ASA-class (2 strata: ASA≤2 and ASA=3) and
- investigational centre

Stratification variables will be included as covariates in the primary analysis (according to CPMP/EWP/2863/99).

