| Title of Study              | PROSPECTIVE, CONTROLLED, DOUBLE-BLIND, RANDOMIZED MULTICENTRIC STUDY ON THE EFFICACY AND SAFETY OF TARGET CONTROLLED VOLUME REPLACEMENT THERAPY WITH A HYPERONCOTIC BALANCED HES 130/0.42 SOLUTION VS AN ISOONCOTIC BALANCED HES 130/0.42 SOLUTION COMPARED TO A BALANCED ELECTROLYTE SOLUTION IN ELECTIVE SURGERY OF THE PANCREATIC HEAD                                                                                                                                                                                                                                                                                                                                                                                                                                                                                       |
| Investigational Products    | 
Investigational Test Product:
 
Tetraspan 10% (hyper-oncotic balanced HES 130/0.42 solution)
 
Investigational Reference Product:
 
Tetraspan® 6% (iso-oncotic balanced HES 130/0.42 solution)
 
Descriptive control:
 
Sterofundin ISO (balanced electrolyte solution)
 
A treatment group receiving solely a crystalloid/electrolyte volume replacement is included in the study as in various hospitals and countries respectively this treatment is still a standard in surgery including pancreatic surgery. As crystalloid solutions, however, display another volume effect*, than colloidal solutions (*thus leading to a distinct higher requirement of volume which could be easily recognised even when blinded) this treatment group will only serve as a descriptive control.
 |

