## **8 STUDY DESIGN**

This is a prospective, randomized, controlled, double-blind, multi-centre phase IV study performed in three parallel groups.

Comparison will be made of a hyper-oncotic (10%) balanced HES 130/0.42 solution with an iso-oncotic (6%) balanced HES 130/0.42 solution on the basis of a multiple endpoint. The principle of ordered hypothesis will be used [see section 16 statistics]

for testing the two primary endpoints: “the intra-operative amount of colloidal volume replacement therapy during target directed volume replacement therapy” (first), subsequently “days until fully on oral solid diet” (second).

A third treatment arm (as a descriptive control) will comprise the administration of solely a balanced crystalloid fluid replacement. This group is included in the study as in various hospitals and countries respectively volume replacement solely with electrolytes is still a standard in surgery including pancreatic surgery. As crystalloid solutions, however, display another volume effect\* than colloidal solutions (\*thus leading to to a distinct higher requirement of volume which could be easily recognised even when blinded) this treatment group will only serve as a descriptive control.

The study will be started with an internal pilot phase which serves for recalculation of sample size for the first primary variable respectively for ensuring sufficient power for the second primary variable. Interim analysis will also serve for deciding of premature termination of the study for futility. This interim analysis will be performed by estimating the pooled variances for both primary endpoints without unblinding [see section 16 statistics].

In the first phase of the study (internal pilot phase) the number of patients is 20 (including drop-outs) for each treatment arm.

Beside this two-phase design with a number of 60 patients in the pilot phase, a rough estimation of the sample size (for the 1st primary variable) to expect resulted in:

69 patients per group, supposing an effect size (difference of means)/(common standard deviation) =  $\frac{1}{2} = 0.5$ , error of the 1st kind  $\alpha = 5\%$  (two-sided), Power = 80% and the nonparametric Mann-Whitney U-Test (Calculations with nQuery Advisor, version 6.0). Taking a drop-out rate of 10% into consideration, a sample size of 76 patients per group will be needed.

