This sample size also should be sufficient for the 2nd primary variable (for details see section 16)

Estimated total sample size:

Internal pilot phase

[figure not shown]

The study will be performed in three study centres in Berlin and Bonn, Germany.

\*\* may change according to calculation of pooled variance after internal pilot phase.

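### Printing the block sizes while calling the crystalloid arm recognisable lets a site predict HES versus crystalloid somewhat better than chance

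*Protocol*

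**What the plan says.** Protocol section 9.5 states "Patients will be randomized to either treatment in a 1:1:1 ratio". The list is generated "considering the stratification for investigational centre and ASA-class" (ASA II or below, and ASA III), and its structure is given as a "random permuted block of size 3, 6 or 9". Each patient's random number carries the centre, the ASA stratum and a running number within that stratum, and enrolment is logged separately for the two strata. A site can therefore see where it stands in each of its lists.

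Section 8 places the trial in three centres. It makes the crystalloid arm a descriptive control because of its "distinct higher requirement of volume which could be easily recognised even when blinded". The synopsis gives the same reason.

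On the protective side, section 9.5 says: "The list will be prepared prior to the initiation of the study and will remain with the statistician". The hospital pharmacy allocates and masks the product, and every arm receives the same number of bottles for a given body weight. The protocol does not say whether the three sizes are mixed at random within a list or whether one size is chosen for it.

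**The concern.** Permuted blocks are predictable to anyone who knows the block sizes and can identify earlier allocations. Here the sizes are in the document that the sites work from, and the protocol itself says that one arm could be identified. A site that has just seen one or two crystalloid patients in a stratum has reason to think the next will be HES.

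The risk is selective enrolment. Section 14.1 places inclusion and randomisation between day -5 and day -1, so there is some discretion over whom to enter and when. Selection of this kind could distort the comparison of HES with crystalloid. That comparison is descriptive, but it is part of the secondary objectives in section 7.2 and is the trial's only randomised view of HES against no HES for renal function, coagulation and blood loss. The planned covariates are centre and ASA class only, so the analysis would not repair it, and section 19.1.3 appoints no safety monitoring board.

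**Working it through.** **Inputs from the protocol.** Ratio 1:1:1, so 1/3 crystalloid and 2/3 HES. Block sizes 3, 6 and 9. Three centres by two ASA strata give 6 lists. Planned total 228 (69 per group × 1.1 = 75.9, rounded to 76; 3 × 76 = 228), so 228/6 = 38 patients per list if the lists are equal. The protocol gives no figure for predictability, so there is none to reproduce.

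**Assumptions.** An ideal observer knows the sizes and the past HES/crystalloid sequence in the stratum. Accuracy of recognising each patient as HES or crystalloid: 100%, then 90% and 80%. Use of sizes: either drawn at random with probability 1/3 each, or one fixed size. The protocol settles none of these.

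**One fixed size.** A block of size b holds c = b/3 crystalloid and h = 2b/3 HES allocations. An allocation is certain once the other type is exhausted. The expected number of certain allocations per block is h/(c+1) + c/(h+1).

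- b = 3: (2/2 + 1/3)/3 = 44.4% certain
- b = 6: (4/3 + 2/5)/6 = 28.9% certain
- b = 9: (6/4 + 3/7)/9 = 21.4% certain

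Best guesses are right 77.8%, 74.4% and 72.8% of the time. Always saying HES is right 66.7% of the time.

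**Sizes mixed at random.** The observer's chance of crystalloid next is the sum over possible block states of w × r_c/(r_c + r_h). Here w is the current weight of a state, and r_c and r_h are the crystalloid and HES allocations left in it. The weights are updated after each patient.

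Example at the start of a list: the first patient is recognised as crystalloid. The chance that the second is also crystalloid is 0/2 for size 3, 1/5 for size 6 and 2/8 for size 9. The average is (0 + 0.20 + 0.25)/3 = 15%, against 33% unconditionally. Later in a list the position within the block is less clear, and one preceding crystalloid patient alone lowers the chance only to about 22% to 23%.

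Simulation of lists of 38 patients. AUC is the probability that a crystalloid enrolment had a higher predicted chance of crystalloid than an HES enrolment; 0.5 means no information.

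| Recognition | Enrolments with chance ≤ 15% | Certain | Best guess right | AUC |
|---|---|---|---|---|
| 100% | 34% | 3.6% | 73.3% | 0.77 |
| 90% | about 2% | 0% | 68.0% | 0.65 |
| 80% | 0% | 0% | 66.8% | about 0.6 |

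Under perfect recognition, crystalloid actually follows in about 10% of the low-chance enrolments. A further 17% of enrolments carry at least a 50% chance, and about 70% of these are crystalloid. Lists of 12 give similar figures (31%, 17%, AUC 0.76).

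**What the remedies achieve (perfect recognition).**

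- Sizes withheld, with the observer treating 3, 6, 9, 12 and 15 as equally likely (an assumption): the share at or below 15% falls from 34% to about 10%, no allocation is certain, and AUC stays near 0.76.
- Sizes 6, 9 and 12 instead, still known: that share falls to 18% and AUC to 0.73, while the share with at least a 50% chance stays at about 18%.

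**The case against.** The 34% rests on error-free recognition of every earlier patient, and the protocol reports no recognition rate. Volume is titrated to each patient's stroke volume. Section 16.4 admits that volume requirements in this surgery are not reliably known. The later bottles in the 10% arm are themselves crystalloid, and any arm can move to open-label crystalloid when its bottles run out. At 90% recognition most of the effect is gone. This stands, and the 34% must be read as an upper bound.

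Naming three sizes also suggests that they vary, which is a guard against prediction. That is the more natural reading, though the text does not fix it.

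The list is held centrally, the pharmacy allocates, two anaesthetists are separated to protect blinding, and a screening log covers all patients considered. Nothing says that whoever enrols patients tracks intraoperative volumes by stratum. These points make selective enrolment less likely. They do not address prediction from known sizes plus a recognisable arm.

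A reader might infer that upcoming allocations can often be guessed. The figures do not support that for mixed sizes: about 4% are certain, and the best guess gains 6 to 7 points over always saying HES. A reader might also infer that the primary comparison is compromised. Nothing in the protocol says that 10% and 6% HES can be told apart, and knowing that the next patient is HES does not say which.

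**Conclusion.** The point holds as a modest, avoidable weakness in allocation concealment for HES versus crystalloid. The protocol publishes the block structure and also says that one arm could be recognised, and no other section cures the combination.

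The size depends on two things the protocol leaves open. With sizes mixed at random the advantage ranges from 73% against 67% correct guesses (perfect recognition) to almost nothing (80% recognition). With one fixed size, 21% to 44% of allocations would be certain under perfect recognition. Whether any site would act on this cannot be judged from the protocol.

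The confirmatory tests of 10% against 6% HES are largely spared. What is exposed is the descriptive comparison with crystalloid, including renal and coagulation safety.

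**What to change.** Delete the block sizes from section 9.5. State there only that block sizes vary at random within each centre-by-ASA list, and keep the sizes in the statistician's restricted randomisation specification. This costs a wording change, provided that the list already varies the sizes at random.

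Optionally avoid size 3, for example by varying 6, 9 and 12. That needs a regenerated list before the start and allows slightly larger imbalance within a stratum.

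Neither step makes allocation unpredictable. Blocked 1:1:1 allocation with a recognisable arm stays partly predictable even when the sizes are withheld, so the change should be presented as a cheap reduction of the risk. No endpoint, sample size or clinical procedure is affected.

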## **10 INVESTIGATIONAL PRODUCTS**

Appropriate amount of the Investigational Products will be made available to hospital pharmacist by B. Braun Melsungen AG. If defects in the Investigational Products are observed, the study manager or the monitor is to be informed.

### **10.1 Name and Description of the Investigational Product(s)**

#### **10.1.1 Qualitative and Quantitative Composition**

The following table presents the composition of the Investigational Products, i.e.

1000 ml solution contains:

|                                          | Investigational Test Product                                                                       | Investigational Reference Product                                                                | Descriptive Control Investigational Reference Product                          |
|------------------------------------------|----------------------------------------------------------------------------------------------------|--------------------------------------------------------------------------------------------------|--------------------------------------------------------------------------------|
|                                          | Tetraspan 10%                                                                                      | Tetraspan 6%                                                                                     | Sterofundin ISO                                                                |
|                                          | hyper-oncotic solution of HES 130/0.42/6:1 in plasma adapted Ringer's solution (balanced solution) | iso-oncotic solution of HES 130/0.42/6:1 in plasma adapted Ringer's solution (balanced solution) | plasma adapted Ringer's solution (balanced electrolyte (crystalloid) solution) |
| Ingredients/ per 1L               |                                                                                                    |                                                                                                  |                                                                                |
| HES 130/0.42                             | 100 g                                                                                              | 60 g                                                                                             | --                                                                             |
| sodium chloride                          | 6.25 g                                                                                             | 6.25 g                                                                                           | 6.80 g                                                                         |
| potassium chloride                       | 0.30 g                                                                                             | 0.30 g                                                                                           | 0.30 g                                                                         |
| calcium chloride dihydrate               | 0.37 g                                                                                             | 0.37 g                                                                                           | 0.37 g                                                                         |
| magnesium chloride hexahydrate           | 0.20 g                                                                                             | 0.20 g                                                                                           | 0.20 g                                                                         |
| sodium acetate trihydrate                | 3.27 g                                                                                             | 3.27 g                                                                                           | 3.27 g                                                                         |
| malic acid                               | 0.67 g                                                                                             | 0.67 g                                                                                           | 0.67 g                                                                         |
| Electrolyte concentrations per 1L |                                                                                                    |                                                                                                  |                                                                                |
| sodium                                   | 140.0 mmol                                                                                         | 140.0 mmol                                                                                       | 140.0 mmol
145.0 mmol*                                                      |
| potassium                                | 4.0 mmol                                                                                           | 4.0 mmol                                                                                         | 4.0 mmol                                                                       |
| calcium                                  | 2.5 mmol                                                                                           | 2.5 mmol                                                                                         | 2.5 mmol                                                                       |
| magnesium                                | 1.0 mmol                                                                                           | 1.0 mmol                                                                                         | 1.0 mmol                                                                       |
| Chloride                                 | 118.0 mmol                                                                                         | 118.0 mmol                                                                                       | 127.0 mmol/l                                                                   |
| acetate                                  | 24.0 mmol                                                                                          | 24.0 mmol                                                                                        | 24.0 mmol                                                                      |
| malic acid                               | 5.0 mmol                                                                                           | 5.0 mmol                                                                                         | 5.0 mmol                                                                       |
| Further characteristics           |                                                                                                    |                                                                                                  |                                                                                |
| pH                                       | 5.6 – 6.4                                                                                          | 5.6 – 6.4                                                                                        | 5.1 – 5.9                                                                      |
| theoretical osmolarity                   | 297 mOsmol/l                                                                                       | 297 mOsmol/l                                                                                     | 309 mOsmol/l                                                                   |
| titration acidity                        | < 2.0 mmol/l                                                                                       | < 2.0 mmol/l                                                                                     | ~ 5 mmol/l                                                                     |

For HES an inhouse-specification applies while all other ingredients are in accordance to the European Pharmacopoeia (Ph. Eur.).

The Investigational Products will be manufactured and released by the Sponsor B. Braun Melsungen AG, Melsungen, Germany in compliance with Good Manufacturing Practice (GMP). For batch number and expiry date see certificate of analysis.

